### Intervention protocol

2.3

The study consists of a 12-week intensive intervention phase followed by a 12-week follow-up phase. This 12-week duration is chosen based on evidence that significant cognitive and neuroplastic changes in MCI populations typically manifest within 3 months of rTMS and structured exercise (e.g., dance) (Guo et al., 2025; Sánchez-Alcalá et al., 2025). While a 24-week intervention was considered, the 12-week model is preferred to maximize participant retention and minimize “intervention fatigue” in this elderly population, while still being sufficient to demonstrate synergistic effects (Ren et al., 2025). The subsequent 12-week follow-up will allow for the assessment of the durability of these effects—a critical factor for clinical translation. Participants will be supervised by trained instructors and medical staff.

#### rTMS intervention (active and sham)

2.3.1

Participants in the Combined Intervention and rTMS Only groups will receive active rTMS. Sessions will be conducted 5 days per week for the first 4 weeks (induction phase), followed by 2 sessions per week for the remaining 8 weeks (maintenance phase). Each session will involve intermittent theta burst stimulation (iTBS) over the left dorsolateral prefrontal cortex (DLPFC). The iTBS protocol consists of bursts of 3 pulses at 50 Hz, repeated at 5 Hz. A total of 600 pulses will be delivered per session (2 seconds on, 8 seconds off, for 190 seconds) at 70–80% of the individual’s resting motor threshold (rMT). A 7-cm figure-of-eight coil connected to a magnetic simulator will be used, with neuronavigation to ensure consistent targeting.

For participants in the Combined Intervention group, the sequence and timing of the two modalities are strictly controlled to maximize the neuroplastic priming effect. The iTBS will always be administered prior to the DMI. Following the completion of the 3-minute iTBS session, participants will commence the DMI within a strict 10- to 15-minute window. This specific timing interval is chosen based on neurophysiological evidence demonstrating that a single block of iTBS induces a transient state of enhanced cortical excitability and long-term potentiation (LTP)-like plasticity that peaks shortly after stimulation and lasts for approximately 20 to 30 minutes (Huang et al., 2005; Tse et al., 2018). Initiating the cognitively and physically demanding dance routines within this critical time window ensures that the activity-dependent neuroplasticity driven by the DMI coincides with the iTBS-induced state of heightened cortical receptivity, thereby optimizing the synergistic therapeutic effects (Stoykov and Madhavan, 2015).

Participants in the DMI Only and Control groups will undergo a sham rTMS procedure. A placebo coil that produces an equivalent sound and scalp sensation without inducing a therapeutic magnetic field will be used to maintain blinding.

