Previous studies have demonstrated that rTMS, particularly when applied to the dorsolateral prefrontal cortex (DLPFC), a region critical for executive function and memory, can improve cognitive performance in individuals with MCI (Guo et al., 2025; Yuan et al., 2025). Recent comparative trials indicate that iTBS over the left DLPFC yields cognitive benefits equivalent to conventional high-frequency rTMS in MCI, while requiring only a fraction of the session time (e.g., 3 vs. 37.5 minutes) (Zheng et al., 2024). rTMS can also modulate functional connectivity within key brain networks, such as the default mode network (DMN) and fronto-parietal network, which are often disrupted in MCI (Esposito et al., 2022; Guo et al., 2025). By directly influencing neural circuits and promoting synaptic plasticity, rTMS may prime the brain to be more receptive to subsequent cognitive and behavioral interventions in MCI. Among various forms of physical activity, dance stands out as a particularly rich, multi-faceted intervention for older adults with MCI. Dance—particularly structured forms such as Chinese square dancing—integrates physical, cognitive, social, and emotional components, offering benefits beyond conventional aerobic exercise (Colcombe and Kramer, 2003; Tao et al., 2023; Wu et al., 2022). It improves cardiovascular fitness, balance, gait speed, and motor coordination, all vital for maintaining physical independence and reducing fall risk in MCI (Sánchez-Alcalá et al., 2025). Learning and executing complex dance sequences demand continuous attention, working memory, planning, and decision-making, providing intensive cognitive training, while synchronizing movements to music and partners further challenges dual-tasking abilities and cognitive flexibility (Quan et al., 2025). Group dance activities foster social engagement and a sense of community—reducing loneliness and isolation, which are known risk factors for cognitive decline and depression in MCI (Cacioppo and Cacioppo, 2018)—while the accompanying music, rhythmic movements, and expressive elements can enhance mood, reduce stress, and provide multisensory input that supports brain health and emotional regulation (Hewston et al., 2021). Chinese square dancing, with its energetic rhythms and group format, is particularly well-suited to delivering these benefits, as it is easy to learn, affordable, and highly popular among older adults in China (Ou et al., 2022).

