### Trial design

2.1

This study will adopt a four-arm, single-blinded, parallel-group randomized controlled trial (RCT) design, chosen to comprehensively evaluate the individual and synergistic effects of repetitive transcranial magnetic stimulation (rTMS) and a dance movement intervention (DMI). Participants will be randomly assigned in a 1:1:1:1 ratio to one of four parallel groups: (1) a Combined Intervention Group, receiving active rTMS followed by the DMI (Chinese Square Dance); (2) an rTMS Only Group, receiving active rTMS and a time-matched, non-aerobic social activity control; (3) a DMI Only Group, receiving sham rTMS followed by the DMI; and (4) a Control Group, receiving sham rTMS and the social activity control. The research protocol will adhere to the Standard Protocol Items: Recommendations for Interventional Trials (SPIRIT) guidelines (Chan et al., 2013) and the Consolidated Standards of Reporting Trials (CONSORT) statement for non-pharmacologic treatments (Barbour et al., 2017), and the study will be conducted in accordance with the Declaration of Helsinki (Association, 2025) and has been registered at Chinese Clinical Trial Registry (ChiCTR2600127655). All procedures will be carried out at the Department of Rehabilitation, Handan Central Hospital, Handan, China (see **Figure 2**).

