Warm-up (10 min) — stepping combined with breathing, head movement, spinal side-bending, and turning exercises.DMI choreography (30 min) — three structured routines performed in unison to music; the third routine includes interactive movements with partners.Break (5 min) — seated rest and water intake.DMI improvisation (15 min) — the instructor performs movements at the front of the group; participants may follow along, dance independently, or engage in interactive movements with partners.Cool-down (5 min) — slow stretching and breathing, combined with low-speed stepping.Social sharing (10 min) — facilitated group discussion in which each participant is invited to use one or two words, a gesture, or a movement to express their feelings, enjoyment, and playfulness regarding the dance experience, and to share words of encouragement or care with one another.

These six steps aim to encourage the participants to remember steps and sequences; concentration and memory will be required to perform this dance routine smoothly and correctly; improve mood and vitality, foster imagination and creativity. In addition, attention and planning movement in space with the aim of using movement activities and paying attention to bodily experiences to improve cognitive function. Furthermore, personal expression (verbal and non-verbal) to enhance communication and social exchange, respectively. For treatment fidelity, before the intervention, two instructors will teach two classes as practice for dance intervention groups. Every class will last one hour, with a one-day gap between the two classes. In these sessions, researchers will explain the essentials of DMI—including the six-component class structure (warm-up, choreography, break, improvisation, cool-down, and social sharing), safety guidelines (footwear, hydration, permission to rest in a seated position at any time, and the principle that movements need not be 100% accurate), and use of the post-class practice video—together with its potential health benefits for older adults with MCI, including improvements in motor function (balance, coordination, cardiovascular fitness), cognitive function (attention, working memory, motor planning, executive function), social engagement, and emotional well-being. Participants will then be introduced to basic movements through guided practice with instructor feedback.

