#### Social activity control

2.3.3

To control for the social interaction and general engagement inherent in the DMI, participants in the rTMS Only and Control groups will attend time-matched sessions (60 minutes, 3 times per week) involving non-aerobic activities such as watching educational videos, listening to music, and engaging in supervised, non-strenuous group discussions.

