##### Factorial analysis for synergistic effects

2.9.1.3

To directly address the study’s aim of elucidating synergistic mechanisms and to capitalize on the robust factorial design, a 2 × 2 factorial analysis will be nested within the models. The main effect of the rTMS factor (active vs. sham), the main effect of the DMI factor (active vs. sham), and the rTMS × DMI interaction effect on the primary outcome will be tested. A statistically significant positive interaction term will quantitatively support the hypothesis that the combined intervention produces benefits exceeding the additive effects of the individual modalities.

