### Social engagement and cultural accessibility

3.3

The group-based, culturally familiar format of Chinese square dancing is hypothesized to address social isolation, a modifiable risk factor for cognitive decline (Read et al., 2020), by combining physical activity with structured social interaction. Observational data further suggest an association between long-term Chinese square dancing and preserved cognitive performance in older adults (Zhao et al., 2024); the present trial, however, is not designed to isolate the social contribution from the rTMS effect.

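### The 10- to 15-minute gap after iTBS is set for the Combined arm only, so the rTMS × DMI interaction may mix dance with session timing

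*Protocol article*

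**What the plan says.** Section 2.3.1 gives the delivery rule and says to whom it applies: "For participants in the Combined Intervention group, the sequence and timing of the two modalities are strictly controlled". Stimulation always comes first, and then "participants will commence the DMI within a strict 10- to 15-minute window". The reason given is that the after-effect of one iTBS block lasts about 20 to 30 minutes and dance should coincide with it.

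Section 2.1 describes the other arms. DMI Only has an order, with sham before dance, but no interval. The second arm is "an rTMS Only Group, receiving active rTMS and a time-matched, non-aerobic social activity control", which sets neither order nor interval. Control is described in the same way, with sham in place of active stimulation.

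Section 2.3.3 spells out the time-matching of the social sessions as three 60-minute sessions a week. That is length and frequency, not position relative to stimulation. The stated purpose of these sessions is "To control for the social interaction and general engagement inherent in the DMI".

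Section 2.9.1.3 then tests the rTMS × DMI interaction on the primary outcome: "A statistically significant positive interaction term will quantitatively support the hypothesis" that the combination exceeds the sum of its parts.

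**The concern.** The interaction isolates the joint effect of the two factors only if the cells differ in those two factors and in nothing else that matters. The plan treats the interval after stimulation as an active part of the treatment, yet sets it in one cell of four. The arm that matters most is rTMS Only, the only other arm given active iTBS. As written, Combined and rTMS Only differ in dance versus social activity. They may also differ in whether any group session falls soon after active stimulation.

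At stake is what a positive interaction can be attributed to. If engagement of any kind soon after iTBS carried a benefit, that benefit would be present in Combined and might be absent in rTMS Only. The social control would then not fully do its stated job of absorbing social interaction and general engagement.

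**Working it through.** The plan gives no figure of its own on this point, so the check has three parts: what each arm is told to do, how a timing effect passes through the contrast, and where a timing rule can apply.

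**1. The arms side by side** (Sections 2.1, 2.3.1, 2.3.3)

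| Arm | Stimulation | Group session | Order stated | Gap stated |
|---|---|---|---|---|
| Combined | active | dance | iTBS first | 10 to 15 min |
| rTMS Only | active | social | none | none |
| DMI Only | sham | dance | sham first | none |
| Control | sham | social | none | none |

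**2. The contrast.** Let the Control mean be m, the rTMS effect a, the DMI effect b, and the synergy specific to dance s.

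- Interaction = (Combined − DMI Only) − (rTMS Only − Control).
- With no timing effect: (a + s) − a = s.
- Add an effect d of having any group session soon after active iTBS. If only Combined has it: (a + s + d) − a = s + d.
- If both active arms have it: (a + s + d) − (a + d) = s.

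So d enters with weight 1 when timing is unmatched and cancels when it is matched. Under the plan's priming rationale the sham arms carry no d. Their timing matters only for uniform delivery.

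The documents give no value for d. As an illustration only, take s = 0, assume that rTMS Only never benefits from the window, and express d in SDs of the outcome. The standard error of the contrast is √(4/n) for n per arm. Here n = 40 as randomised, and 160 × 0.80 / 4 = 32 after the 20% attrition of Section 2.7. The probability of a two-sided p < 0.05 is Φ(d/SE − 1.96) + Φ(−d/SE − 1.96):

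| Assumed d (SD) | n = 32 | n = 40 |
|---|---|---|
| 0 | 0.050 | 0.050 |
| 0.1 | 0.059 | 0.062 |
| 0.2 | 0.087 | 0.097 |
| 0.3 | 0.136 | 0.158 |
| 0.5 | 0.293 | 0.353 |

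These rows show what an assumed d would do. They are not evidence that d exists.

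**3. Where a rule can apply.** iTBS sessions: 5 × 4 + 2 × 8 = 36. Group sessions: 3 × 12 = 36. With at most one of each per day, the shared visits are at most 3 × 4 + 2 × 8 = 12 + 16 = 28, so at least 36 − 28 = 8 group sessions have no iTBS that day. This shows the reach of the rule. It does not measure a difference between arms.

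**The case against.** Four points can be made against this.

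First, this could be called an omission. An article condenses the protocol, Section 2.6.1 refers to standard operating procedures, and nothing says that the intervals differ between arms. It stands that no difference in delivery is shown. But the article does not stay silent on timing. It states the rule in detail, justifies it, and restricts it by its own words to one factorial cell.

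Second, the premise is unproven. Section 2.3.1 ties the window to demanding dance routines, whereas the social sessions are videos, music and quiet discussion. This stands in large part, and it is why the point is conditional. It is not decisive, because the Introduction puts the priming idea more broadly: "rTMS may prime the brain to be more receptive to subsequent cognitive and behavioral interventions in MCI".

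Third, the plan credits a positive interaction to the combination, not to dance as such, and timing is part of the Combined regimen. That protects any comparison of the regimen as delivered. It does not protect the factorial reading. Timing is not one of the two factors, and Section 3.1 says that the design is meant to separate their contributions.

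Fourth, matching the timing is not free. One iTBS session lasts 190 seconds and the allowed start spans 15 − 10 = 5 minutes, or 300 seconds. With one stimulator and no set-up time (both assumptions), sessions ending at 0 and 190 seconds fit, and a third ending at 380 does not. So two participants could share one start time, against dance classes of up to 10. This stands and belongs in the cost.

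**Conclusion.** The point holds in a limited, conditional form. The gap is set for Combined only. DMI Only has an order but no gap, and the two social arms have neither. If social or general engagement is sensitive to timing after active iTBS, a positive interaction could not be attributed to dance rather than to any activity soon after stimulation. Neither the existence nor the size of that sensitivity can be obtained from the documents.

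A reader might infer more, and the documents do not support it:

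- That the iTBS-first order is also fixed for Combined alone. Section 2.1 puts sham before dance in DMI Only.
- That the interaction is biased, or that intervals will differ in practice. No section says so.
- That Section 3.3 already admits the problem. It says "the present trial, however, is not designed to isolate the social contribution from the rTMS effect", which concerns the social element and not the interval after stimulation.
- That the Combined regimen cannot be compared with the other arms. As delivered, it can.

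This is a worthwhile improvement to the delivery rules, not a flaw that invalidates the design. It has to be made before delivery, because timing cannot be matched in the analysis afterwards.

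**What to change.** Replace the Combined-only rule in Section 2.3.1 with one rule for every visit on which both sessions occur (at most 28 of the 36 group sessions): stimulation first, then the group session 10 to 15 minutes later. The change that matters is in rTMS Only, where the social session should follow active iTBS exactly as dance does in Combined. Use the same order and gap with sham in DMI Only and Control so that delivery is uniform. Keep the same weekly pairing of stimulation and group days in all arms; otherwise a rule tied to shared visits may still leave the arms unmatched.

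Record the interval in every arm: one extra field in the dance adherence log of Section 2.3.2, and a short equivalent record for the social sessions. If operating procedures already set this timing, one sentence saying so is enough.

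The cost is tighter scheduling of individual iTBS slots before group sessions, possibly with smaller or staggered social groups. No extra visits or participants are needed, and the sample size does not change.

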#### Dance movement intervention

2.3.2

Participants in the Combined Intervention and DMI Only groups will participate in a structured Chinese Square Dancing program. Sessions will be held 3 times per week for 12 weeks, with each session lasting 60 minutes. The intervention emphasizes rhythm, coordination, memory of sequences, and social interaction. Participants in this group will receive in total thirty-six hours of intervention. A maximum of 10 participants will be enrolled in each DMI class to ensure performance quality. Instructors will use oral explanations and encouragements during the interventions.

Chinese square dancing movement programs have been applied within various populations showing evidence of benefits (Bisbe et al., 2020; Blumen et al., 2022; Zhu et al., 2018, 2022). Any 4 × 4 beats music can be used for dance intervention routine; participants will also be allowed to recommend music. The DMI will combine choreography and improvisation, single and partner strategies, including gentle body movements (consisting of limbs and spine movements) with special emphasis on rhythm and contralateral movement on both sides of the body to enhance coordination and stimulation between right and left cerebral hemispheres (Ho et al., 2015, 2020). The DMI routine contains repetition and improvisation; therefore, it will require memory, concentration and dual-task function to complete the dance correctly.

The dance moves are gender-neutral and applicable to both males and females. Dance routines will be adapted to participants’ abilities, and new routines may be introduced every three to four weeks. Each session will be led by one dance instructor positioned at the front of the group, who will lead the dance and encourage social connection. A second instructor and supporting medical staff will supervise participants’ movements, guide correct execution, and ensure safety. The DMI targets both motor participation and specific cognitive processes. At the motor level, the choreographed and improvised routines are designed to engage whole-body coordination, balance, and cardiovascular demand. At the cognitive level, the routines are designed to engage attention, working memory, motor planning, and executive function—through memorizing step sequences, synchronizing movements to music, adapting to changing choreographic patterns, and engaging in partner-based interactions. Participants are not required to perform movements with 100% accuracy; rather, the emphasis is on sustained engagement with both the motor and cognitive demands of the task, in order to experience the body as a source of creativity and reliability. A practice video featuring standard movements will be provided after each class to support at-home familiarization. Rest periods, during which participants may sit and drink water, are built into each session. To accommodate older participants, the dance intervention can be performed in seated positions when needed to reduce fatigue. Intervention fidelity and adequate involvement will be documented session-by-session using a structured adherence log completed by the supervising instructor. The log will capture: (i) session attendance and duration of active participation; (ii) instructor-rated movement engagement and quality on a 5-point Likert scale; (iii) proportion of the session completed in standing versus seated position; and (iv) any adverse events or safety concerns. These data will be used to characterize intervention delivery and to support per-protocol analyses.

Each dance class will consist of six structured components, delivered in the following sequence:

Warm-up (10 min) — stepping combined with breathing, head movement, spinal side-bending, and turning exercises.DMI choreography (30 min) — three structured routines performed in unison to music; the third routine includes interactive movements with partners.Break (5 min) — seated rest and water intake.DMI improvisation (15 min) — the instructor performs movements at the front of the group; participants may follow along, dance independently, or engage in interactive movements with partners.Cool-down (5 min) — slow stretching and breathing, combined with low-speed stepping.Social sharing (10 min) — facilitated group discussion in which each participant is invited to use one or two words, a gesture, or a movement to express their feelings, enjoyment, and playfulness regarding the dance experience, and to share words of encouragement or care with one another.

These six steps aim to encourage the participants to remember steps and sequences; concentration and memory will be required to perform this dance routine smoothly and correctly; improve mood and vitality, foster imagination and creativity. In addition, attention and planning movement in space with the aim of using movement activities and paying attention to bodily experiences to improve cognitive function. Furthermore, personal expression (verbal and non-verbal) to enhance communication and social exchange, respectively. For treatment fidelity, before the intervention, two instructors will teach two classes as practice for dance intervention groups. Every class will last one hour, with a one-day gap between the two classes. In these sessions, researchers will explain the essentials of DMI—including the six-component class structure (warm-up, choreography, break, improvisation, cool-down, and social sharing), safety guidelines (footwear, hydration, permission to rest in a seated position at any time, and the principle that movements need not be 100% accurate), and use of the post-class practice video—together with its potential health benefits for older adults with MCI, including improvements in motor function (balance, coordination, cardiovascular fitness), cognitive function (attention, working memory, motor planning, executive function), social engagement, and emotional well-being. Participants will then be introduced to basic movements through guided practice with instructor feedback.

A sign-in system will be implemented for each class during the investigation, and a small gift or daily necessities (towel, soap, toothbrush, etc.) will be awarded to those participants who attended intervention sessions. The aim of training monitoring is to check exercise interventions’ training intensity. The interventions will be conducted as moderate intensity, based on levels of perceived exertion. Participants will be instructed to carry out their intervention activities without exceeding 4–6 points on the Borg Scale (0 to 10 scale) (Borg, 1982). Instructors will regularly ask participants about their perceived fatigue levels during activities and help them to maintain the target level of effort.

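### The six timed parts of a dance class add up to 75 minutes, but the session and its time-matched social control are both set at 60 minutes

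*Protocol article*

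**What the plan says.** Section 2.3.2 fixes the dance schedule: "Sessions will be held 3 times per week for 12 weeks, with each session lasting 60 minutes". It then gives the total: "Participants in this group will receive in total thirty-six hours of intervention".

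Later the same section sets out the content of a class: "Each dance class will consist of six structured components, delivered in the following sequence". The list that follows times each part: warm-up 10 minutes, choreography 30, break 5, improvisation 15, cool-down 5 and social sharing 10. Just before the list, the section says of rest: "Rest periods, during which participants may sit and drink water, are built into each session".

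Section 2.3.3 gives the two non-dance arms social sessions of 60 minutes, three times per week. It calls them time-matched and says their purpose is to control for the social and engagement content of the dance programme. Section 2.1 also describes the control as time-matched. Section 2.9.1.3 tests the main effect of dance on the primary outcome.

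**The concern.** The class as itemised is longer than the session that is meant to contain it. The social control is matched to the stated session length, not to the itemised one.

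The social control is there to take general contact and engagement out of the dance effect. If participants attend 75 minutes against 60, the dance arms have more total contact, and that excess cannot be separated from the dance main effect or from the dance-versus-social contrasts. The issue is total contact time. The control arms already have group discussions, so a missing discussion component is not the complaint.

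If the class really lasts 60 minutes, contact is balanced, but a different problem remains: instructors cannot deliver the list as printed, and the article does not say what gives way. Two instructors could make different cuts and deliver different amounts of movement.

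Class length is the same in the combined and dance-only arms, so the discrepancy does not by itself create an rTMS × DMI interaction.

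**Working it through.** **Inputs.** Section 2.3.2: 3 sessions per week, 12 weeks, 60 minutes, 36 hours in total, and the six component times. Section 2.3.3: social sessions of 60 minutes, 3 per week. Section 2.1 and the Figure 2 legend: 40 participants per arm.

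**The plan's own total.** Sessions = 3 × 12 = 36. Hours = 36 × 60 / 60 = 36. The stated 36 hours follows from the stated session length.

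**The session from its components.** 10 + 30 + 5 + 15 + 5 + 10 = 75 minutes. Over 36 sessions, 36 × 75 / 60 = 45 hours. The 60 minutes is not reproduced. The excess is 15 minutes per session, 45 − 36 = 9 hours in total, and 45 / 36 = 1.25, or +25%.

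**Three possible readings.**

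| Reading | Dance contact | Social contact | What fails |
|---|---|---|---|
| 60 min is the whole class | 36 h | 36 h | The list is 15 min too long |
| 60 min is movement time only | 45 h | 36 h | Time-matching |
| The class runs as itemised | 45 h | 36 h | Stated length, total hours and time-matching |

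The second reading has some arithmetic behind it: warm-up, choreography, improvisation and cool-down give 10 + 30 + 15 + 5 = 60 minutes, leaving break plus sharing at 5 + 10 = 15. But the text counts both of these among the six parts of the class and places rest inside the session.

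**Movement time if the class is held to 60 minutes.** The list contains 60 minutes of movement. What remains depends on where the 15 minutes are cut. Dropping whole components:

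| Removed | Movement left per session | Over 36 sessions |
|---|---|---|
| Break + sharing | 60 min | 36 h |
| Cool-down + sharing | 55 min | 33 h |
| Warm-up + break | 50 min | 30 h |
| Improvisation, or warm-up + cool-down | 45 min | 27 h |

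**Practice classes.** Section 2.3.2 adds two one-hour practice classes for the dance groups before the intervention, 2 × 1 = 2 hours. Assuming the social arms have no counterpart (the article describes none), contact is (36 + 2) / 36 = 1.056, or +6%, at 60 minutes, and (45 + 2) / 36 = 1.306, or +31%, at 75 minutes. The conclusion does not depend on these figures.

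**Side check on stimulation pairing.** Section 2.3.1 gives iTBS on 5 days per week in weeks 1–4 and twice per week in weeks 5–12, against three dance sessions per week throughout. Dance sessions that can follow iTBS: min(5, 3) × 4 = 12 of 12, then min(2, 3) × 8 = 16 of 24, so at most 28 of 36.

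**The case against.** The strongest reply is that this is a slip in the list. The 60 minutes appears in both 2.3.2 and 2.3.3 and reproduces the 36 hours, so it is probably the intended length. Scheduled contact is then balanced and the repair is a matter of wording. That is plausible, and it is why the default fix below keeps 60 minutes. It does not remove the problem: the printed sequence still cannot be delivered in that time, and the planned movement content is not settled.

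A second reply is that the movement components sum to exactly 60 minutes, so the authors may have meant 60 minutes of dance. The article does not say so, and participants would still attend 75 minutes against 60 in the control.

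A third reply is that the instructor's log in 2.3.2 records attendance and active time session by session, so the delivered dose will be known. This is true and useful, but a record of what was delivered does not set what was planned, and it does not equalise contact between arms.

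It is also fair to say that nothing here shows how far extra contact would move MoCA, and that the practice-class percentages rest on a condensed article's silence about the social arms. Both points stand as limits on the size of the finding.

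**Conclusion.** The concern holds. The component times, the 60-minute session and the time-matched 60-minute control cannot all be true under any of the three readings.

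If the list is delivered, or if 60 minutes means movement only, contact is 45 against 36 hours (+9 hours, +25%) in favour of the dance arms. If 60 minutes is the whole class, contact is 36 against 36 hours, and planned movement time ranges from 27 to 36 hours. These figures cover scheduled sessions with full attendance.

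The consequence for the dance effect is therefore conditional on 75 minutes being attended, and its size on MoCA is unknown. Sample size, alpha, power and the interaction test are untouched. It should be corrected before classes begin, because it fixes both the intervention and its comparator. The stimulation-pairing count is a point for clarification, not an error.

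**What to change.** 1. Set one total session length in 2.3.2 and make the component list and total hours agree with it. The default is to keep 60 minutes and 36 hours and shorten the list by 15 minutes, naming the components that lose time. If 75-minute classes are intended, state 75 minutes and 45 hours.
2. Give the social control in 2.3.3 the same total contact time per session: no change at 60 minutes, 75 minutes if that is chosen.
3. As a clarification, add a sentence to 2.3.1 saying that iTBS comes before dance on days when both are given, so at most 28 of 36 dance sessions are iTBS-paired (12 of 12 in weeks 1–4, 16 of 24 in weeks 5–12).

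**Cost.** At 60 minutes, wording only. At 75 minutes, each social session is 15 minutes longer: 36 × 15 / 60 = 9 hours per participant, and 9 × (40 + 40) = 720 participant-hours over the two social arms. Neither option adds visits or changes the stimulation or dance schedule.
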